## Discussion

This trial aims to propose a possible efficacious treatment for initial caries lesion on approximal surfaces, which could be useful in private and public contexts representing an easier and effective option to treatment of enamel approximal caries in children and adolescents.

In theory, it is known that initial caries lesions could be arrested by biofilm removal [36]. In fact, dental flossing would be the simplest procedure for biofilm removal to control initial lesions on approximal surfaces. However, this control depends on correct and frequent flossing by patients [3], which could explain the difficulty in arresting lesions in these specifics areas [6]. When flossing is not effective, it is necessary to resort to other possibilities to control caries lesions. That is why it is important to evaluate flossing comparatively to other available options in order to seek for the simplest and most cost-efficacious/effective treatment.

Previous studies evaluated the preventive effect of SDF [22] and/or its efficacy on dentine lesions [7, 37]. However, few studies assessed its efficacy on initial caries lesion [8, 9]. In addition, no previous study verified its application on approximal surfaces. A systematic review showed that SDF seems to be more effective than fluoride varnish [38]. A possible explanation for this superior effect could be the fluoride concentration on SDF, which is higher than that found in the fluoride varnish [39]. However, the effect of SDF on caries lesions could be explained not only by fluoride action, but also by the silver ions, which react with thiol groups in amino and nucleic acids leading to bacterial lysis [38], and thus to probable quicker caries arrestment [8, 40], especially if compared to other options of arresting initial caries lesions such as other fluorides.

There are some aesthetic concerns regarding the use of SDF since it could cause black staining on carious lesions due to the precipitation of silver [38]. However, aesthetics did not seem to be jeopardized in the case of initial caries lesions on approximal surfaces of posterior teeth due to their localization. However, the staining could be a limitation of our study regarding examiners’ blinding, since it could suggest which surfaces were treated with SDF. Nevertheless, inactive lesions could also present dark coloring, minimizing this limitation [8, 22].

On the other hand, resin infiltration is a new procedure, with promising results, but it could be costly and be less accepted by patients. Previous studies have shown that flossing is less effective than infiltration, sealing, and other fluoride treatments [13, 14, 41, 42]. To the best of our knowledge, there is no study that has previously compared flossing, which would be the simplest technique to be used on approximal surfaces, with SDF. As children/adolescents who will be enrolled in this study live in an area of fluoridated water and regularly use fluoridated toothpaste, if we had not included the control group, we could not affirm which is the actual simplest and most cost-efficacious technique for approximal initial caries, which is why we decided to conduct this study in three-arm parallel groups rather than design a non-inferiority trial comparing just SDF with resin infiltration. However, depending on the results of this study a posterior effectiveness trial could be conducted. Besides, all children have been exposed to daily fluoride, have been motivated to floss every day, and are monitored regularly. Therefore, we believe that using flossing as a control group has not compromised the ethics of the trial.

To compare these three interventions, we considered important the use of placebo therapies to ensure that interventions are as similar as possible among individuals. If individuals are aware of which group they will be allocated to, they may judge more complex techniques, which demands a lot of clinical steps, as more effective and underestimate the correct daily flossing in these cases. Due to the vulnerable individuals [43] included in our study, the perfect placebo therapies could be questionable. Thus, for ethical issues, the placebo of resin infiltration will be performed just simulating the rubber dam on teeth, without local infiltration anesthesia and clamp. Despite being an imperfect placebo, simple measures like this can be enough to blind patient regarding adopted treatment [44]. Therefore, in such a type of imperfect placebo-controlled study, we expect that daily flossing is not influenced by the intervention received.

On the other hand, we must consider that sequential treatments may influence patients’ perception about the treatment. Because of its sensitivity to light, a light-curing or light curing simulation will have to be applied after the use of SDF. Thus, the sequence has been standardized and our option was to apply the faces scale at the end of all procedures, and not only after the active treatment, despite the latter being ideal. The use of the scale only after active treatment would compromise the blinding, which would be worse. In addition, using the procedures in sequence will make the sessions longer. Therefore, we believe we should discuss our results considering that a session for application of SDF on initial approximal caries lesions would certainly consume less time than will be presented in the results of this trial. A pilot study is ongoing to check the partial times for each approach separately and the influence of each individual treatment and their respective placebos on patient perception.

Finally, we should expect a degree of memory bias, especially a named choice-supportive bias [45] when we checking daily flossing. Actually, children and adolescents, as well their parents/guardians, may be conscious of the correct flossing behavior [46], especially in a study like ours, since they are orientated to act in a specific way during a certain time. Therefore, they could report the daily use of dental floss, regardless of this being the case. This bias could underestimate the actual efficacy of this practice and should be considered when interpreting our findings.

At the end of this study we expect to contribute to point out the option(s) which would be definitely more efficacious/cost-effective than the mechanical removal of biofilm from approximal surface by flossing.

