### Study design

This is a randomized clinical trial, double-blinded, placebo-controlled study conducted in three-arm parallel groups. The participants will be allocated to one of the three arms in order to compare different options for arresting initial caries lesions (Figure 1). The participants and their parents/guardians, as well as the examiners, will not be aware of the patient’s allocation.

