### Primary outcome

A single trained, calibrated, and blinded examiner ([name]) will assess caries lesions progression by direct visual exam using ICDAS and an adjunct index to assess caries lesion activity status [23]. The ICDAS score and the activity status will be assessed after tooth separation for at least 48 hours. The main outcome considered will be caries progression to evident dentine cavitated caries lesion. Bitewing radiographs will be taken to evaluate possible caries progression into dentin according to Ekstrand et al. [15]. The progression detected by radiographs or by ICDAS scores transition, as well as changes in the caries lesion activity status, will be considered as possible surrogate outcomes.

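### SDF staining may partly unmask the single visual examiner and could make active SDF lesions look arrested, so activity change should not stand in for cavitation

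*Protocol article*

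**What the plan says.** **Blinding.** The Study design section says that participants and parents, "as well as the examiners, will not be aware of" the allocation. The Primary outcome section gives the scoring to "A single trained, calibrated, and blinded examiner".

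**Method of assessment.** That examiner works by "direct visual exam using ICDAS and an adjunct index to assess caries lesion activity status". The surface is exposed first: "The ICDAS score and the activity status will be assessed after tooth separation for at least 48 hours". Follow-up examinations places the visual examination at 6, 12 and 24 months and the radiographs at 12 and 24 months.

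**Outcomes.** The main outcome is progression to evident dentine cavitation. Three measures are listed as possible surrogates: radiographic progression, transitions in ICDAS score, and "changes in the caries lesion activity status". The Statistical analysis section allows surrogates into the efficacy models where they are needed.

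**Staining.** The Discussion says of SDF that "it could cause black staining on carious lesions due to the precipitation of silver". It accepts that this may limit examiner blinding, "since it could suggest which surfaces were treated with SDF", and then answers that "inactive lesions could also present dark coloring, minimizing this limitation".

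**The concern.** Two separate problems follow from the stain, and the article's reassurance addresses only the first.

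- **Unmasking.** An examiner who sees a black lesion may infer the arm. The blinding statements in Methods carry no such qualification.
- **Misclassification.** Even an examiner who never thinks about allocation may take a dark lesion to be inactive. Stain from the treatment is confined to the SDF arm, so this error would be differential. It would run towards the option that the authors expect to be the most cost-efficacious.

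At stake is activity status. Lesions must be active at entry and the aim is to arrest them, so a change to inactive is the most literal reading of success. It is also one of the surrogates that the plan allows into the efficacy models.

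**Working it through.** No stated figure is in dispute, so the main check sets the sections side by side.

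1. **Can the examiner see the stain?** Yes, if it occurs. The Discussion argues that the position of these surfaces limits the aesthetic harm. Tooth separation before scoring opens the same surfaces to direct view, so their position does not protect the blind.
2. **How far does one stained surface reach?** Random allocation assigns individuals, and Inclusion criteria enters every eligible surface of a patient. One recognisable stain can therefore suggest the arm for all of that patient's surfaces.
3. **Does the reassurance restore the blind?** Only if dark lesions are about as common in the other two arms. The article does not claim that.
4. **Does it protect activity scoring?** No. If inactive lesions tend to be dark, a dark stain resembles inactivity. The premise used to reassure about unmasking makes misreading more plausible.
5. **Which outcomes are exposed?** Activity status most, visual ICDAS transitions less, and evident cavitation least, although the same examiner scores all three. Bitewings do not show surface colour. They are taken at 12 and 24 months, so the 6-month visit rests on vision alone, while the hazard ratios use all follow-up times.

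**Illustration only.** The inputs below are assumptions, not figures from the article. Let p be the share of lesions truly active in both arms, with no true difference, and s the share of active SDF lesions recorded as inactive because of colour. The SDF arm then shows p × (1 − s) active, and the false difference is p − p × (1 − s) = p × s. For p = 50% and s = 20% this is 50% − 40% = 10 points.

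| p | s = 10% | s = 20% | s = 30% | s = 40% |
|---|---|---|---|---|
| 30% | 3 points | 6 | 9 | 12 |
| 50% | 5 points | 10 | 15 | 20 |
| 70% | 7 points | 14 | 21 | 28 |

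With the article's 86 surfaces per group before inflation, a two-sided 5% test and clustering ignored, the chance of a false significant result favouring SDF at p = 50% is about 10%, 26%, 51% and 77% across the four columns. At p = 30% it is about 6%, 14%, 27% and 45%. At p = 70% it is about 16%, 48%, 81% and 97%. The table shows how the error would scale. It does not estimate how large it is here.

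**The case against.** The strongest reply is that nothing here shows a bias. The article says that SDF could stain and that inactive lesions could be dark. That some inactive lesions are dark does not mean that dark lesions are scored inactive. That step depends on the criteria of the activity index, which the article cites but does not reproduce. The enrolment examination is both visual and tactile, so colour may not decide the score. This stands: the point is a risk with a clear direction and unknown size.

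Second, the main outcome is cavitation, and a stain does not imitate the absence of a cavity. This also stands. What remains for cavitation is the general loss of masking.

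Third, the limitation is disclosed. That is true, and there is no concealment. But the disclosure ends in a reassurance that does not cover activity scoring, and the Methods statements stay unqualified.

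Fourth, a reader might infer that activity change is set to displace cavitation. The text does not say so: activity is one of three possible surrogates, to be used only if needed. The route is open, not chosen.

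Finally, a reader might set a false difference of 20 points against the 20% difference in the sample size section. That comparison is unsupported, because the section does not tie its 20% to activity status and the inputs behind the 20 points are assumed.

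**Conclusion.** The concern holds as a risk of bias. On the article's own account, examiner blinding cannot be assumed for SDF surfaces, so the unqualified statements in Study design and Primary outcome claim too much. The appeal to dark inactive lesions does not protect activity scoring, where a misreading would favour SDF.

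The size cannot be given. It depends on how often SDF stains these lesions, how much weight the activity index gives to colour, and how common dark lesions are in the other arms. None of these is in the article.

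Two stronger readings are not supported. The documents do not show that the activity results are biased, and they do not show that the cavitation result is invalid. Nor is there a case for making radiographic progression the confirmatory outcome: the authors class it as a surrogate, and it measures something other than evident cavitation. The article does not say how the films are read or by whom. That is a detail an article may leave to the full protocol and is not held against it.

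**What to change.** 1. **Study design and Primary outcome:** describe examiner blinding as partial for SDF surfaces because of possible staining.
2. **Primary outcome and Statistical analysis:** state that activity change will not be used in place of cavitation for efficacy. Report it descriptively, by arm, as potentially unmasked.
3. **Statistical analysis:** pre-specify radiographic progression on the bitewings already planned at 12 and 24 months as a supporting sensitivity analysis for SDF against infiltration and SDF against flossing. Code the films and have them read without knowledge of arm or clinical findings. Keep cavitation as the main outcome.
4. **Discussion:** limit the remark about dark inactive lesions to the question of unmasking, and add that it does not remove the risk to activity scoring.

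The cost is some coding of films, one added analysis and the loss of activity change as an efficacy surrogate. No extra visit, film or procedure is needed.

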## Trial status

This is an ongoing trial, which is still recruiting the patients at this moment.

## Authors’ original submitted files for images

Below are the links to the authors’ original submitted files for images. Authors’ original file for figure 1 Authors’ original file for figure 2

## Abbreviations

CI: Confidence interval
DMFS: Decayed, missing, filled surfaces in permanent teeth
Dmfs: Decayed, missing, filled surfaces in primary teeth
ICDAS: International Caries Detection and Assessment System
SDF: Silver diamine fluoride.
